# Study protocol: fish oil supplement in prevention of oxaliplatin-induced peripheral neuropathy in adjuvant colorectal cancer patients – a randomized controlled trial. (OxaNeuro)

**DOI:** 10.1186/s12885-024-11856-z

**Published:** 2024-02-03

**Keywords:** Chemotherapy-induced peripheral neuropathy, Oxaliplatin, Colorectal cancer, Fish oil, Omega-3 fatty acids, Neurofilament light, Inflammation, Specialized proresolving mediators, Quality of life, Randomized controlled trial

## Abstract

**Background:**

Oxaliplatin-induced peripheral neuropathy (OIPN) in general and painful OIPN in particular is a debilitating late effect that severely affects cancer survivors’ quality of life and causes premature cessation of potentially lifesaving treatment. No preventive treatments and no effective treatment for chronic OIPN exist despite many attempts. One of several suggested mechanisms includes neuroinflammation as a contributing factor to OIPN. Fish oil containing long-chain n-3 polyunsaturated fatty acids (n-3 LCPUFAs) are precursors to specialized proresolving mediators that mediate the resolution of inflammation. Our primary hypothesis is that a high supplementation of n-3 LCPUFAs will lower the prevalence and severity of OIPN.

**Methods:**

The OxaNeuro project is an investigator-initiated, multicenter, double-blinded, randomized, placebo-controlled clinical study. We will include 120 patients eligible to receive adjuvant oxaliplatin after colorectal cancer surgery. Patients will receive fish oil capsules containing n-3 LCPUFAs or corn oil daily for 8 months.

The primary endpoint is the prevalence of OIPN at 8 months defined as relevant symptoms, including one of the following: abnormal nerve conduction screening, abnormal vibration threshold test, abnormal skin biopsy, or abnormal pinprick test. Additional endpoints include the intensity and severity of OIPN-related neuropathic pain, patient-reported OIPN symptoms, quality of life, mental health symptoms, body composition, and cognitive evaluation. Furthermore, we will evaluate inflammatory biomarkers in blood samples and skin biopsies, including the potential OIPN biomarker neurofilament light protein (NfL) which will be measured before each cycle of chemotherapy.

**Discussion:**

If readily available fish oil supplementation alleviates OIPN prevalence and severity, it will significantly improve the lives of both cancer survivors and palliative cancer patients receiving oxaliplatin; it will improve their quality of life, optimize chemotherapeutic treatment plans by lowering the need for dose reduction or premature cessation, and potentially increase survival.

**Trial registration:**

ClinicalTrial.gov identifier: NCT05404230

Protocol version: 1.2, April 25^th^. 2023

**Supplementary Information:**

The online version contains supplementary material available at 10.1186/s12885-024-11856-z.

## Background

Symptoms of chemotherapy-induced peripheral neuropathy (CIPN) are generally described as primarily sensory symptoms with a stocking and glove distribution comprising loss of sensation, para- or dysesthesia, and/or pain [1]. CIPN comprises heterogeneous subgroups characterized by varying prevalence and phenotypical manifestations, contingent upon the specific neurotoxic chemotherapy employed [2].

Oxaliplatin-induced peripheral neuropathy (OIPN) is seen in an acute and a chronic version. Acute OIPN occurs in 85-95% of patients receiving oxaliplatin [3]. It is characterized as an acute cold allodynia in the extremities and perioral area. Symptoms occur shortly after treatment and normally dissolve within the following week [4, 5]. The chronic version affects over half of patients receiving oxaliplatin, of whom 20% experience neuropathic pain [6]. Chronic OIPN is a dose- and length-dependent peripheral neuropathy that develops during and often after ended treatment (coasting), where patients report loss of sensation, persistent para- or dysesthesia and/or pain primarily in the feet [6–8]. Cramps and muscle weakness can also be seen in patients [9, 10]. Chronic OIPN, including neuropathic pain, is a disabling condition known to severely affect cancer survivors’ quality of life and is often associated with other problems, such as loss of function, anxiety, depression, and disturbed sleep. Chronic OIPN is associated with a significant human and economic burden on health resources [11, 12].

Despite numerous efforts, no proposed treatments have successfully prevented or effectively managed CIPN [13, 14]. Duloxetine is the only medication that has shown some effect on painful CIPN, but its estimated effect size is low, and the treatment is not without side-effects [15, 16].

Several biomarkers have been assessed in an attempt to find a valid predictor of CIPN [17]. Neurofilament light polypeptide (NfL) is a structural protein shed from neurons upon neuroaxonal damage to the bloodstream. This protein has been proven useful as a biomarker in several neurological diseases, e.g., multiple sclerosis, stroke, and Alzheimer's disease [18]. NfL has been found to correlate with evaluated symptoms of CIPN in smaller, primarily observational, studies including breast cancer or gynecological cancer, with patients receiving taxanes [19–23]. Only one study measured NfL in patients with OIPN symptoms; however, this study measured the level of NfL at fixed time points 3 and 6 months after baseline [24]. To our knowledge, we are the first to examine NfL levels in patients receiving oxaliplatin in a prospective manner before each cycle of oxaliplatin, with a relevant population size and long-term follow-up. This design allows us to evaluate the use of NfL as a predictive biomarker and explore if both acute and chronic CIPN affect the level of NfL.

The mechanism of acute OIPN is altered sodium ion channels which produce peripheral nerve hyperexcitability [25–27]. However, the mechanism of chronic OIPN is not known in detail, albeit several overlapping theories have been proposed. One such dominant theory is that mitochondrial damage is induced by oxidative stress in the dorsal root ganglia (DRG), which is not protected by the blood and brain barrier, causing neuronal degeneration [2]. However, neuroinflammation and modulation of the immune response have been shown to be relevant mechanisms of the pathogenesis of OIPN and the development of neuropathic pain [28]. Several studies have demonstrated an increased innate neuroimmune response and proinflammatory cytokine expression following chemotherapy exposure [29]. In preclinical studies, these changes have been shown to be associated with sensitization and hyperexcitability in peripheral nerves primarily mediated by satellite glial cells surrounding the DRG [30, 31].

Long-chain n-3 polyunsaturated fatty acids (n-3 LCPUFAs), such as docosahexaenoic acid (DHA, 22:6n-3) and eicosapentaenoic acid (EPA, 20:5n-3), have been shown to be potent inflammation inhibitors in animal and cell models [32]. In clinical trials, DHA and EPA have been shown to alleviate chronic inflammatory diseases, such as rheumatic arthritis, by reducing the need for non-steroid inflammatory drugs (NSAIDs) [33]. Additionally, in the acute setting of sepsis, cytokine levels and length of hospital stay were positively affected by DHA and EPA [34].

In cancer patients receiving n-3 LCPUFAs from fish oil supplements, inflammatory cytokines, including interleukin- 6 (IL-6), C-reactive protein (CRP) and tumor necrosis factor-alpha (TNFα), were found to be lower than those in control groups [35]. Eicosanoid-like molecules derived from n-3 LCPUFAs and n-6 LCPUFAs play a crucial role in signaling between immune cells during the inflammatory process. Proinflammatory eicosanoids, such as prostaglandins, thromboxanes and leukotrienes, primarily derived from arachidonic acid (AA, 20:4n-6), are upregulated by early inflammatory stimuli and mediate the initiation of the inflammatory process. The n-3 LCPUFAs, on the other hand, are main precursors for specialized pro-resolving mediators (SPM), resolvins, maresins, and protectins. These SPMs actively mediate downregulation and resolution of the inflammatory process [34]. Hence, an intake of fish oil supplements containing n-3 LCPUFAs increases concentrations of SPMs in peripheral blood and mediates translational changes in immune cells [36]. However, the exact mechanisms of SPMs remain unclear and multifaceted. SPM has also been investigated in the context of neuropathic pain [37]. In this context, a few clinical studies have shown promising results of dietary n-3 LCPUFAs on prevention of CIPN, which should be tested in a larger trial [38–40].

DHA is essential for optimal development and functioning of the nervous system [32, 41], and n-3 LCPUFAs have been shown to affect cognitive development [42]. Some studies have observed beneficial effects on cognitive decline [43], and a meta-analytic review found a significantly positive effect of n-3 LCPUFAs on depression. However, the effect of n-3 PUFAs on cognition during and after chemotherapy has not been evaluated.

N-3 LCPUFAs and chemotherapeutic treatment has been studied with various focus throughout the years. To date no negative interactions between n-3 LCPUFAs and chemotherapy have been reported. Conversely, some preclinical studies indicate a synergistic relationship between the two in certain settings [44, 45].

The primary aim of this study is to evaluate whether a daily intake of a high dosage of fish oil containing n-3 LCPUFAs reduces the prevalence and severity of OIPN and neuropathic pain 8 months after adjuvant oxaliplatin following surgery for high-risk colorectal cancer. Additional aims are to investigate whether n-3 LCPUFAs influence body composition, cognition, and mental status. Furthermore, we want to study the inflammatory mechanism of OIPN in skin biopsies and blood and explore potential early predictive biomarkers of OIPN, particularly NfL.

### Design and methods

Project OxaNeuro is an investigator-initiated, multicenter, double blinded, randomized placebo-controlled clinical trial. Patients are randomized to one of two arms: fish oil capsules or identical corn oil capsules for 8 months in total.

The study comprises daily intake of capsules, six visits, neurological and sensory examination, questionnaires, skin biopsies and blood sampling. Five of the six visits are scheduled together with planned visits at the Department of Oncology. Adjuvant chemotherapy is concluded after visit four, but the patients will continue with the daily intake of the trial supplements for a total of 8 months. During the follow-up period, patients will receive two phone calls to monitor compliance. The last visit (visit 5) is planned after 8 months, and this concludes the trial period (Fig. 1).

**Fig. 1 Fig1:**
[figure not shown]
Project OxaNeuro flowchart. Flowchart of the OxaNeuro project. Each blue box represents a patient contact in the project comprising either personal appearance or phone call. One visit (visit 5) is not scheduled together with the planned visits at the Department of Oncology

### Study population and eligibility

Patients diagnosed with colorectal cancer, operated, and referred to one of four participating Departments of Oncology at University Hospital of Southern Denmark Vejle, University Hospital of Southern Denmark Soenderborg, Aarhus University Hospital, and Aalborg University Hospital are eligible. Patients meeting the inclusion criteria (Table 1) will be invited to participate and provide written informed consent.

**Table 1 Tab1:** Inclusion and exclusion criteria

Inclusion criteria	Exclusion criteria
• Histopathologically verified adenocarcinoma of the colon or rectum and planned standard adjuvant treatment with capecitabine in combination with oxaliplatin • Age ≥ 18 • ECOG performance status 0-2 (measurement of a patient’s function in terms of self-care, daily activity and physical ability) [46] • Written and orally informed consent.	• Inability to speak, read, and understand Danish • Previous treatment with neurotoxic chemotherapy • Neurological (including neuropathy) or psychiatric disorders, diabetes, or other significant medical conditions • Alcohol or drug abuse • Sensory disturbances in the feet • Spinal stenosis • Vascular disease (Fontaine grade II or more) • Known allergy to fish, fish oil or corn oil • Fertile patients not willing to use effective methods of contraception during treatment or abstinence • Daily intake of oil supplements and not willing to stop during the trial period • Lack of consent to skin biopsy

ECOG: Eastern Cooperative Oncology Group

Dietary intake of LCPUFAs in the Danish population is low and thus not expected to affect the trial. Therefore, dietary intake is not documented, and specific diets are not cause for exclusion [47, 48].

If patients experience verified disease relapse, they will be withdrawn from the trial. Dose reduction or premature cessation of oxaliplatin is not cause for exclusion if the patient has received at least one dose of oxaliplatin.

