### Compliance

Compliance will be monitored continuously through verification and registration by a study nurse at each visit. The excess capsules will be counted, and patients will be asked about their compliance at each visit. During the trial two phone calls will be placed with the purpose of compliance and patient retention.

Furthermore, in a subgroup, we will evaluate compliance in blood samples taken at three different time points (visits 1, 4 and 5, see Fig. 1). The n-3 LCPUFA content in erythrocyte membrane is measured as an objective measure of compliance. The samples will be analyzed by high-throughput fatty acid analysis by gas chromatography with flame ionization detection using Varian 3900 or Agilent 7890A instruments [49]. Samples are stored and shipped in bulk for analysis at the Laboratory of Nutritional Lipidomics, Department of Kinesiology and Health Sciences, Faculty of Health, University of Waterloo, Canada.

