### Statistical analysis and sample size

The present study will compare the treatment outcomes of patients in the two arms.

Based on previous studies we expect an OIPN prevalence of 50% in the control group and estimate a prevalence in the fish oil group to be 23%, which is a clinically meaningful difference [6, 39, 63]. Using 80% power and 5% risk of type I error, the sample size estimate is 49+49 patients for the primary objective. To account for dropouts, the project will include 120 patients, with 60 patients in each group.

Patient demographics and baseline characteristics will be described using descriptive statistics. Continuous variables will be summarized according to their distribution with medians and interquartile range (IQR) or means and standard deviations (sd). Categorical variables will be summarized with frequencies and percentages.

The primary endpoint (OIPN) is a dichotomous endpoint defined by the developed definition of OIPN. The two independent proportions of OIPN in the two randomization arms will be compared using the chi^2^ test and reported as frequencies and percentages with corresponding p-values. P-values <0.05 will be considered statistically significant. All analyses will be performed as intention-to-treat (ITT). In case of cross-over between study arms due to non-compliance, per protocol analyses will be performed as sensitivity analyses to explore the potential bias from the non-compliance. In per-protocol analyses, non-compliance will be defined using an 80% percent cut-off or a significant lack of DHA and EPA rise in compliance blood samples.

The proportion and patterns of missing data will be explored, and in the case of <5% missing data, analyses will be performed as complete case. If the amount of missing data is comprehensive (>5%) or suggestive of biased estimates, appropriate methods of imputation will be applied depending on the patterns of missingness.

A complete statistical analysis plan covering each outcome will be developed together with statistical consultant [name] M.Sc., PhD. Statistical analyses will be performed using STATA version 18 (STATA Corp., Texas, USA) and all steps of data management, coding and analyses will be logged.

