## Discussion

Project OxaNeuro is a strong randomized, double blinded, placebo-controlled study including a solid biobank on this well-defined group of patients for future research. By defining OIPN and OIPN related neuropathic pain by evaluating both large and small nerve fibers and objectively evaluating nerve fiber density together with relevant symptoms we obtain a comprehensive evaluation of OIPN. We adhere to current guidelines for defining neuropathic pain developed by the International Association of the Study of Pain Special Interest Group on Neuropathic Pain (NeuPSIG) and can establish neuropathic pain in these patients with a high level of certainty [64]. Due to a lack of consensus on the definition and evaluation on chemotherapy induced neuropathy as well as the significant overlap in symptoms, our setup is based on the expert consensus on defining and evaluating diabetic neuropathies [65].

N-3 LCPUFAs have been studied for different purposes preclinically and in several groups of cancer patients, including patients receiving concomitant chemotherapy, and there have been no reports of inferior antineoplastic results in the groups receiving n-3 LCPUFAs [45, 66, 67]. Furthermore, a study comprising almost 26,000 patients found no excess risk of bleeding, cardiovascular events, cancer, or other serious adverse events in patients receiving n-3 PUFAs compared to controls [68]. To achieve the anti-inflammatory effect and pain relief as observed in patients with rheumatoid arthritis, the ratio of EPA/DHA must exceed 1.5 [33]. Additionally, Dempsey et al recommend a combined dosage of EPA and DHA of at least 1000-15000 mg/day for a minimum of 12 weeks to measure elevated levels of EPA and DHA in blood samples [69]. The chosen n-3 LCPUFA dosage in the OxaNeuro project of 2 g EPA and 1 g EPA is based on these data, and the dosage is significantly higher than that in comparable studies [38–40]. However, the European Food Safety Authority (EFSA) reports that a combined daily intake of up to 5 g of DHA and EPA is considered safe for adult consumption [70].

Because fish oil is a supplementation readily available to purchase in various convenience stores, we chose to make the evaluation of compliance objective and thereby more reliable by measuring compliance via blood samples. In the field of supplementation studies, this method is regarded as the benchmark for evaluating compliance [71].

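### The oil-supplement exclusion leaves non-daily fish-oil users eligible with no stated need to stop, and the blood-based compliance rule would not identify them in the corn-oil arm

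*Protocol article*

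**What the plan says.** The exclusion list in Table 1 (Study population and eligibility) contains the item "Daily intake of oil supplements and not willing to stop during the trial period". Below the table the article argues that n-3 intake from the Danish diet is low, and concludes: "Therefore, dietary intake is not documented, and specific diets are not cause for exclusion". That argument is about food and does not mention supplements.

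The Discussion recognises that patients can obtain the active substance themselves. It opens its case for objective compliance testing with "Because fish oil is a supplementation readily available to purchase in various convenience stores". The Compliance section restricts that testing: "in a subgroup, we will evaluate compliance in blood samples taken at three different time points (visits 1, 4 and 5, see Fig. 1". For all patients, compliance rests on counts of leftover trial capsules, questions about compliance at each visit, and two phone calls.

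The Statistical analysis section makes intention-to-treat the rule and adds: "In case of cross-over between study arms due to non-compliance, per protocol analyses will be performed as sensitivity analyses". For that purpose "non-compliance will be defined using an 80% percent cut-off or a significant lack of DHA and EPA rise in compliance blood samples".

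**The concern.** The exclusion joins two conditions with 'and'. A patient who takes fish oil regularly but not daily fails the first condition and is therefore eligible, and the criterion's requirement to stop does not reach that patient. If randomised to corn oil, the patient could continue own-bought fish oil for the 8 months.

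The comparison is meant to be n-3 supplementation against none. If fish oil works, exposed controls lower the control-arm prevalence of OIPN and bias the primary comparison towards no effect. After a null result, contamination could be checked objectively only in patients with blood data. The per-protocol sensitivity analysis would help little, because its blood criterion describes failure to take fish oil and not unplanned use of it.

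**Working it through.** **1. The criterion, case by case**

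| Patient at screening | Daily? | Unwilling to stop? | Excluded? |
|---|---|---|---|
| Daily user, will not stop | yes | yes | yes |
| Daily user, will stop | yes | no | no |
| Non-daily user, will not stop | no | yes | **no** |
| Non-daily user, would stop | no | no | no, and the criterion does not ask for it |

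The third row is the gap.

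**2. The safeguards against that gap**

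- Capsule counts concern trial capsules only and cannot show own-bought oil.
- Erythrocyte n-3 could show it, but only in the subgroup.
- The per-protocol blood criterion is "a significant lack of DHA and EPA rise in compliance blood samples". A corn-oil patient who takes fish oil would show a rise or a steady high level, so the criterion does not flag that patient, although the sentence before it speaks of cross-over between arms.
- The same criterion can err the other way. A fish-oil patient whose visit 1 level is already high may rise little and be classed as non-compliant despite taking every capsule.

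**3. The plan's sample size**

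Inputs from the Statistical analysis section: 50% (control) against 23% (fish oil), 80% power, 5% type I error (taken as two-sided), 60 per arm enrolled. The formula is the pooled-variance one for two proportions without continuity correction, with mean proportion p̄:

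n = [1.960·√(2p̄(1−p̄)) + 0.842·√(p₁(1−p₁)+p₂(1−p₂))]² / (p₁−p₂)²

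With p̄ = 0.365, 2p̄(1−p̄) = 0.46355; the second variance term is 0.25 + 0.1771 = 0.4271; the difference is 0.27. This gives n = 48.7, so 49 per arm, which matches the article. Power is 80.2% at 49 per arm and 87.7% at 60.

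**4. Illustration of dilution**

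The documents give no rate, dose or frequency of off-trial use. The share c of exposed controls and the fraction e of the full 27-point effect that they receive are assumptions. The fish-oil arm stays at 23%.

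Control prevalence = 0.50 − c·e·0.27

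Power = Φ{[(p₁−p₂)√n − 1.960·√(2p̄(1−p̄))] / √(p₁(1−p₁)+p₂(1−p₂))}

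| c | e | Control prevalence | Power, 49 per arm | Power, 60 per arm |
|---|---|---|---|---|
| 0 | – | 50.0% | 80.2% | 87.7% |
| 5% | half | 49.3% | 78.3% | 86.0% |
| 10% | half | 48.7% | 76.2% | 84.3% |
| 20% | half | 47.3% | 71.8% | 80.4% |
| 5% | full | 48.7% | 76.2% | 84.3% |
| 10% | full | 47.3% | 71.8% | 80.4% |
| 20% | full | 44.6% | 62.1% | 71.1% |

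The 49-per-arm column is the planned evaluable number. The 60-per-arm column assumes no dropout and is an upper bound. The full-effect rows are a worst case.

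**The case against.** The strongest reply is that the size is unknown and likely small. The active dose is 2 g EPA plus 1 g DHA every day for 8 months, and the Discussion describes it as well above that of comparable trials. Someone who takes a shop-bought product less than daily is unlikely to receive the full effect, and even half may be generous. At 5% half-effect exposure the loss is about 2 points of power at 49 per arm. All of this stands, and it is why the full-effect rows should not carry the argument.

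A second reply is that the article condenses a fuller protocol, which may contain instructions on concomitant supplements, and that patients are asked about compliance at every visit and in two calls. This stands in part. The article's silence does not show that non-daily users are never told to stop, or that supplement history goes unrecorded. But the exclusion and the per-protocol rule are stated, and the point rests on their wording.

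A reader might also infer that the lack of a stated washout lets former daily users enter the control arm partly treated. The documents do not support this as a separate fault. A condensed article may leave washout to the full protocol, such patients are randomised to both arms, and carry-over after stopping should wane before the 8-month endpoint. What remains is the possible misclassification of a high-baseline fish-oil patient, which affects only a sensitivity analysis.

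**Conclusion.** The point holds as a weakness in two stated rules. The exclusion does not cover non-daily fish-oil use, and the blood-based compliance rule does not recognise n-3 use in the corn-oil arm. The possible bias in the primary intention-to-treat comparison is towards no effect, if fish oil works.

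On assumed half-effect exposure in 5% to 20% of controls, power is 78% to 72% at 49 per arm and 86% to 80% with all 60 per arm evaluable. These figures rest entirely on the assumed share and effect. A reader might infer that the trial is underpowered or that the contrast is in fact diluted. The documents support neither: the 49 per arm reproduces exactly, and no rate of off-trial use is given. The change is worth making because it is cheap. The article reports 15 of 120 patients included, so most of the planned enrolment could still be covered at that time.

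**What to change.** 1. Reword the exclusion to cover any regular n-3 or fish-oil supplement use, daily or non-daily, that the patient is not willing to stop for the whole trial.
2. Record prior n-3 supplement use at enrolment, and ask about own-bought fish oil at the existing visits and the two compliance calls.
3. Make the per-protocol blood rule arm-specific. In the fish-oil arm, judge compliance on the achieved EPA and DHA level and not on the rise from visit 1. In the corn-oil arm, count a rise or a persistently high level as cross-over.

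The cost is a protocol amendment during recruitment, a few patients who are no longer eligible, and a few data fields. Patients already enrolled will lack the new baseline field. No extra visit or procedure is needed. Outside the blood subgroup, detection will still depend on what patients report.
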